## Abstract

**Background:**

Smartwatches enable continuous and noninvasive time series monitoring of cardiovascular biomarkers like heart rate (from photoplethysmograms), step counter, skin temperature, et cetera; as such, they have promise in assisting in early detection and prevention of cardiovascular disease. Although these biomarkers may not be directly useful to physicians, a machine learning (ML) model could find clinically relevant patterns. Unfortunately, ML models typically need supervised (ie, annotated) data, and labeling of large amounts of continuous data is very labor intensive. Therefore, ML methods that are data efficient, ie, needing a low number of labels, are required to detect potential clinical value in patterns found in wearable data.

**Objective:**

The primary study objective of the ME-TIME (Machine Learning Enabled Time Series Analysis in Medicine) study is to design an ML model that can detect atrial fibrillation (AF) and heart failure (HF) from wearable data in a data-efficient manner. To achieve this, self-supervised and weakly supervised learning techniques are used.

**Methods:**

Two hundred subjects (100 reference, 50 AF, and 50 HF) are being invited to participate in wearing a Fitbit fitness tracker for 3 months. Interested volunteers are sent a questionnaire to determine their health, in particular cardiovascular health. Volunteers without any (history of) serious illness are assigned to the reference group. Participants with AF and HF are recruited in the Haga teaching hospital in The Hague, The Netherlands.

**Results:**

Enrollment commenced on May 1, 2022, and as of the time of this report, 62 subjects have been included in the study. Preliminary analysis of the data reveals significant inter-subject variability. Notably, we identified heart rate recovery curves and time-delayed correlations between heart rate and step count as potential strong indicators for heart disease.

**Conclusion:**

Using self-supervised and multiple-instance learning techniques, we hypothesize that patterns specific to AF and HF can be found in continuous data obtained from smartwatches.

## Introduction

Cardiovascular disease is one of the leading causes of mortality globally^1^ and cardiovascular healthcare accounts for a large portion of global healthcare costs and expenses. Early detection and prevention will decrease the burden of cardiovascular disease and will therefore decrease mortality, morbidity, and costs. Cardiovascular monitoring using big data from wearables and machine learning can drastically increase the availability and efficiency of cardiovascular healthcare globally, at the fraction of the costs of conventional medical-grade devices.

Electrocardiogram (ECG) monitoring, such as Holters or implantable loop recorders, are the gold standard for monitoring of outpatients with known or suspected arrhythmias. However, they are burdensome, can only be used for a limited period of time, and are expensive. Implantable loop recorders are invasive and have to be manually activated and analyzed in the hospital. This severely limits the use of these devices for long-term home monitoring of patients, and they have suboptimal patient comfort. For patients with chronic cardiovascular diseases, such as atrial fibrillation and heart failure, this implies frequent hospital visits and sometimes even hospital admissions (associated with higher mortality) that can be prevented by continuous and adequate home monitoring.

With the widespread availability of reliable, consumer-grade wearables such as smartwatches, continuous monitoring of, for example, heart rate with photoplethysmography and step counting with accelerometers is possible. This monitoring is easy, patient friendly, and cost effective. Combining the power of large amounts of data (big data) and novel machine learning techniques, these time series can be used to detect and perhaps even predict cardiovascular disease, therefore improving patient care. There are some caveats, however, as not all wearables have the same characteristics and quality. Consequently, they have been used with moderate success.^2^^,^^3^ They also provide less informative diagnostic signals as compared to, for example, electrocardiography or other commonly used cardiologic diagnostic modalities. The challenge but also the strength of machine learning models is that they learn by example and therefore large amounts of data are needed for which the cardiovascular outcome (class label) has been determined. Typically, supervised learning is used, where each observation of the data has a class label. This must be done with ECGs, since photoplethysmography or derived signals are difficult to interpret by a clinician. This so-called labeling or annotating of signals by physicians is infeasible for the large amounts of (continuous) data required, and therefore semi-automated^4^^,^^5^ and fully automated^2^^,^^3^ ECG labeling systems^6^ have been developed. However, these still require a lot of manual labor from continuously monitored users.

Therefore, the objective of the ME-TIME is (early) detection and prevention of heart disease by leveraging time series data from smartwatches, a cloud-based infrastructure, and machine learning algorithms specifically designed to function effectively with minimal labeling efforts.

## Methods

### Study design and data collection

ME-TIME (registered at ClinicalTrials.gov; ID: NCT05802563) is designed as an observational cohort study consisting of 3 data subject groups, as depicted in Figure 1. The first group consists of patients with systolic heart failure (HF group); the second group consists of patients with documented atrial fibrillation (AF group); and the third group, serving as a reference, consists of healthy volunteers. The rationale for creating distinct AF and HF groups comes from their unique pathophysiological characteristics. Consequently, heart rate patterns that are indicative of these diseases might also be different. The HF group consists of 50 study participants with systolic heart failure, defined as a left ventricular ejection fraction <35% without documented atrial fibrillation. The AF group consists of 50 patients with documented atrial fibrillation (paroxysmal, persistent, or permanent) without systolic heart failure. Ejection fractions will be assessed from echocardiograms that are made within 1 year of inclusion, and if this is not available an echocardiogram will be performed. The reference group consists of 100 participants without any prior medical history and without medication use. Potential study subjects that meet any of the following criteria will be excluded from participation in this study: age <18 years, age >85 years, recent pulmonary venous antrum isolation (<1 year), kidney or liver failure, known systemic active inflammatory disease, impaired mental state, inability to use a fitness tracker or mobile phone, impaired cognition, and inability to understand the study protocol.

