**Figure 1 fig1:**

Data analysis pipeline for the ME-TIME study. Included participants (image 1) are given a smartwatch (image 2), which is connected to our data acquisition and storage platform (image 3). The resulting data are then preprocessed (image 4) and put into the data-efficient machine learning model (image 5). AF = atrial fibrillation group; HF = heart failure group; Ref = reference group.

Patients will be asked by their treating physician if they may be approached by an investigator to inform them about the study and potential participation. Healthy participants are recruited through local advertising. Anyone that is interested will then receive an information brochure and informed consent form. At least 2 days after the patient’s receipt of the brochure, the research team will call the patient to schedule an appointment. During this visit, the patient submits the signed consent form and will undergo an ECG and blood pressure measurement that will be analyzed by an experienced cardiologist ([name]). Participants can use their own Fitbit and are otherwise provided with a Fitbit Inspire 2 or Fitbit Charge 5 smartwatch. The device type is assigned to a participant at random to prevent device sampling bias. This will also help to investigate the effect of device type on the performance of the final model. A Fitbit account will be created for all participants which will be connected to a custom-built data platform using the Google Cloud Platform. Our platform features a data portal for research staff to easily register or deregister participants by authorizing a connection to their Fitbit data. Data are extracted daily from Fitbits until the observation period ends and can be analyzed either in the cloud or locally.

All participants will be asked to fill out a survey regarding their health. All participants are monitored for a period of 3 months. After written consent from the 200 subjects, heart rate, step counter, and sleep time series data are extracted from the data platform. Clinical metadata such as age, height, weight, blood pressure at baseline, health survey, and medication use are saved in the Castor (Ciwit BV, Amsterdam, The Netherlands) electronic database.

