### MIL can detect healthy cardiovascular outcomes

The peak aligned acceleration-deceleration curves are concatenated with their corresponding step counter data and grouped per week to form bags. The MILES (Multiple-Instance Learning via Embedded Instance Selection) model is then used to classify every week as healthy or AF. The results in Table 2 show that even though the sensitivity is low, the specificity is decent. This shows potential in avoiding unnecessary visits to a cardiologist for patients who have symptoms that are wrongly suspected to be related to heart problems.

**Table 2 tbl2:** Confusion matrix of per-week healthy vs atrial fibrillation classification of the MILES model with peak aligned curves concatenated with step counter data, with true and predicted labels shown vertically and horizontally, respectively

True/Predicted label	AF	Healthy
AF	11	14
Healthy	7	33

AF = atrial fibrillation.

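### Specificity is measured only in healthy volunteers but claimed for people with cardiac-like symptoms, a group the study does not enrol

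*Protocol article*

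**What the plan says.** The protocol article, under Study design and data collection, describes a study "designed as an observational cohort study consisting of 3 data subject groups": systolic HF (LVEF <35%) with no AF on record, documented AF with no systolic HF, and a reference group. On the last it states: "The reference group consists of 100 participants without any prior medical history and without medication use". The Abstract is looser: "Volunteers without any (history of) serious illness are assigned to the reference group". The groups also come from different places: "Healthy participants are recruited through local advertising", whereas "Participants with AF and HF are recruited in the Haga teaching hospital".

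Table 2 gives the preliminary healthy-versus-AF classification by week. The accompanying text calls the sensitivity low and the specificity decent, and sees potential in "avoiding unnecessary visits to a cardiologist for patients who have symptoms that are wrongly suspected to be related to heart problems". The Discussion goes further. It calls the specificity high and useful for ruling out heart disease in people who have similar symptoms but not the disease.

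The Introduction adds that "the objective of the ME-TIME is (early) detection and prevention of heart disease by leveraging time series data from smartwatches". Under Algorithm validation, the external test set is 20% of the enrolled subjects, chosen at random with equal numbers per class.

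**The concern.** Specificity belongs to the non-diseased people in whom it is measured. Here they are well volunteers. The people for whom the benefit is claimed have symptoms and, in practice, often other illness, higher age or medication. Heart-rate recovery, the feature behind the preliminary classifier, could plausibly vary with those factors as well as with AF.

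If the claim stands as written, a reader will take a false-alarm rate seen in healthy volunteers as the rate to expect among people considered for referral. The planned validation would not expose the difference, because its only subjects without heart disease are again volunteers.

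A smaller issue of the same kind concerns early detection. HF cases enter with LVEF <35%, so milder systolic impairment is absent by definition. This does not extend to AF, where paroxysmal disease is included.

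**Working it through.** **1. The stated result.** The article gives counts but no percentage. From Table 2:

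- Specificity = 33 / (33 + 7) = 33/40 = 82.5%; exact 95% interval 67.2% to 92.7%.
- Sensitivity = 11 / (11 + 14) = 11/25 = 44.0%; exact 95% interval 24.4% to 65.1%.

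The unit is the week. Under Study characteristics, data were extracted for 15 healthy and 7 AF subjects, so the 40 healthy weeks come from at most 15 people. The intervals treat weeks as independent and are probably too narrow. The planned outcome is one prediction per subject (Planned machine learning approach), so 82.5% is not the specificity of the planned test.

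**2. Who is in the study and who is in the claim.**

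| Group | Source | Symptomatic but free of AF and HF? |
|---|---|---|
| Reference, 100 | Advertising | No: defined as healthy |
| AF, 50 | Hospital | No: all have AF |
| HF, 50 | Hospital | No: all have HF |

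No group is defined to hold the people named in the claim.

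**3. The external test set.** 20% of 200 = 40 subjects; 40 / 3 ≈ 13 per class. They come from the same three groups, so the set cannot estimate specificity in symptomatic people without heart disease. It does contain AF and HF patients together, so the AF-versus-HF contrast can be examined there.

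**4. How far a specificity can move with the comparator.** Table 1 covers the first 62 subjects. In the reference group 1/25 are aged 65 or over and 2/25 have hypertension. In the AF group the counts are 17/22 and 15/22. Take the rule that anyone aged 65 or over has AF, with no watch data:

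- Sensitivity in the AF group: 17/22 = 77%.
- Specificity in the reference group: 24/25 = 96%.
- Specificity in the HF group, who have no documented AF: 9/15 = 60%.

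This is not an estimate for the article's classifier. It shows, from the study's own data, that a specificity found in these volunteers need not hold in another group without AF.

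**5. Precision of a check in diseased non-cases.** For illustration, if 10 of 13 HF patients in the external set were correctly called not AF, specificity would be 77% with an exact 95% interval of 46% to 95%. About 50 − 13 = 37 patients per disease group remain for cross-validation, so using the folds as well gives more information.

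**The case against.** The strongest reply is that the primary objective in the Abstract is to design a data-efficient model that detects AF and HF. Known cases and healthy volunteers are a reasonable first step for that. The symptomatic use is not an endpoint or a planned analysis, and it is hedged as potential. This stands: the fault lies in the specificity and rule-out claim, not in the study as a whole. But neither the Results nor the Discussion states the limit, and the Discussion strengthens the claim.

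A second reply is that false-positive rates in HF or AF patients do not answer the question either, since these patients have heart disease. That also stands, so such rates are a partial check only. They also need the three-class output described in the caption to Figure 2. Under the heart-disease-versus-healthy scheme in Planned machine learning approach and Box 1, an AF false positive in an HF patient is undefined.

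A reader might infer more than the document supports:

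- That the volunteer specificity is uninformative. It does describe separation of established patients from well people.
- That false positives would rise by some stated factor. Any lower specificity for symptomatic people would be an assumption without support in the article, and 33/40 counts weeks, so it cannot be turned into false alarms per 100 persons.
- That the external test set only repeats the easy contrast. It also includes AF against HF.

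The reference group may not be strictly free of history: the Abstract's wording is looser and Table 1 shows 2/25 with hypertension. Those passages should be reconciled, but the comparator remains healthy volunteers.

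**Conclusion.** The concern holds as a mismatch between claim and comparator. Specificity is measured in healthy volunteers (33/40 weeks, at most 15 subjects) and claimed for symptomatic people without heart disease, whom no group is defined to include and the external test set cannot supply. Specificity in that population is not estimated and cannot be assumed to transfer. A loss is plausible given the age and hypertension differences in Table 1, but its size cannot be computed from the document.

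The conclusion rests on the group definitions and recruitment routes as published and on the external set being drawn from the enrolled subjects. It does not show that the design fails its primary objective. Separately, ruling out disease also depends on sensitivity, and 44% per week would not support that use whichever comparator were chosen.

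**What to change.** - In the Results and Discussion, limit the conclusion to separating documented AF or LVEF <35% from healthy volunteers, and from each other if the three-class model is used.
- Mark the symptomatic rule-out use, and early detection for HF in the Introduction, as needing a separate cohort.
- From the three-class predictions, report subject-level AF false positives in the HF group and HF false positives in the AF group. Give intervals, show them beside the volunteer rate and do not pool them with it.
- Use the cross-validation folds as well as the external set for this, labelled as such because hyperparameters are chosen on those folds.
- Present these rates as a partial check in diseased non-cases, not as specificity in symptomatic people without heart disease.

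No new recruitment is needed; the work is wording and tabulation, provided the three-class output is produced. The downside is a narrower claim and imprecise, probably less favourable, specificity figures.

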### Study characteristics

So far, 62 of the 200 envisioned subjects have been included and data from 22 subjects (15 healthy, 7 AF) have been extracted successfully from the data platform for preliminary analysis (Table 1).

**Table 1 tbl1:** Characteristics of preliminary study participants as of May 2022

Characteristic	Ref	HF	AF
Participants, n	25	15	22
Age, y			
18–39	16	1	0
40–54	3	3	2
55–64	5	5	3
65+	1	6	17
Sex			
Male	12	12	15
Female	13	3	7
BMI			
18.5–24.9	14	3	7
25–29.9	6	6	8
30+	5	6	7
Diabetes			
Yes	0	5	4
No	25	10	18
Smoking			
Yes	0	6	5
No	25	9	17
Hypertension			
Yes	2	8	15
No	23	7	7
Device			
Charge 5	23	8	12
Inspire 2	2	7	10

AF = atrial fibrillation group; BMI = body mass index; HF = heart failure group; Ref = reference group.

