### Heart rate peak alignment in acceleration-deceleration curves indicate difference between 7 AF patients and 15 healthy controls

Next, we explored the heart rate recovery curves after activity (acceleration-deceleration curves).^12^ First a peak is detected, whereafter the start (onset) and end (recovery) points associated to that peak are determined by the minimum heart rate value 5 minutes before and 15 minutes after the peak. The curves are preprocessed by aligning the peaks on the time axis. Additionally, for every subject, the amplitude of the curves is rescaled by the average peak value across all curves for that individual. Figure 6 shows the curves for light activity, defined by a maximum of 20 steps in the 5 minutes preceding the peak and fewer than 10 steps in the 15 minutes after the peak. There are 2 noticeable differences in heart rate patterns between persistent AF patients (in red) and healthy participants (in blue). The standard deviation for AF patients is considerably smaller than that of healthy individuals, and their heart rate recovery is slower, as observed at the 6-minute mark. These distinctions could potentially serve as clinical indicators for atrial fibrillation.

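### Reference volunteers are so far much younger than the AF and HF patients, and because recruitment and validation go by class only, a disease-versus-healthy result cannot be separated from age

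*Protocol article*

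**What the plan says.** Study design and data collection sets the three groups. For patients: "The HF group consists of 50 study participants with systolic heart failure" and "The AF group consists of 50 patients with documented atrial fibrillation". For comparison: "The reference group consists of 100 participants without any prior medical history and without medication use". The Abstract words the last criterion differently: "Volunteers without any (history of) serious illness are assigned to the reference group". Patients are approached through their treating physicians at a hospital. By contrast, "Healthy participants are recruited through local advertising". The only age rule is an exclusion applied to all groups, "age <18 years, age >85 years". Age is stored as metadata, with no analytic use stated.

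Algorithm validation stratifies the cross-validation folds by class. The external test set is a random 20% of subjects with equal numbers per class.

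On progress, Study characteristics reports: "So far, 62 of the 200 envisioned subjects have been included". Table 1 gives their age bands and lists 2 of the 25 reference subjects with hypertension. From 7 AF and 15 healthy subjects, the Results report: "The standard deviation for AF patients is considerably smaller than that of healthy individuals, and their heart rate recovery is slower". These differences are offered as possible clinical indicators of AF, without reference to age.

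**The concern.** The two sides of the main contrast come from different sources under different health requirements. Requiring no history and no medication makes older volunteers hard to find, while AF and HF patients are mostly middle-aged or older. If heart rate recovery or activity patterns change with age, a classifier can tell the groups apart by recognising older people, whether or not it has found anything specific to AF or HF.

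The validation scheme would not expose this. Leaving whole subjects out prevents leakage between training and test data, but held-out reference subjects come from the same pool as the training ones. The internal test set reuses the same people. At stake is the primary objective for disease versus healthy: good performance could not be credited to disease rather than age.

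**Working it through.** **Inputs (Table 1).**

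| Age band | Ref | HF | AF |
|---|---|---|---|
| 18–39 | 16 | 1 | 0 |
| 40–54 | 3 | 3 | 2 |
| 55–64 | 5 | 5 | 3 |
| 65+ | 1 | 6 | 17 |
| Total | 25 | 15 | 22 |

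The totals reproduce the stated count: 25 + 15 + 22 = 62. Sex is also uneven: 12/25 = 48% of reference subjects are male, against (12 + 15)/37 = 73% of patients.

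**1. Separation by age band alone.** The AUC is the probability that a random patient is in a higher band than a random reference subject, with ties counted as one half.

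- AF vs Ref: [2 × (16 + 1.5) + 3 × (19 + 2.5) + 17 × (24 + 0.5)] / (22 × 25) = (35 + 64.5 + 416.5)/550 = 516/550 = 0.94.
- HF vs Ref: [1 × 8 + 3 × 17.5 + 5 × 21.5 + 6 × 24.5] / (15 × 25) = 315/375 = 0.84.
- AF+HF vs Ref: (516 + 315)/(37 × 25) = 831/925 = 0.90.
- AF vs HF: [2 × 2.5 + 3 × 6.5 + 17 × 12] / (22 × 15) = 228.5/330 = 0.69.

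**2. What this means for the full study.** The share of reference subjects aged 65+ is 1/25 = 4%, with an exact 95% confidence interval of about 0.1% to 20%. In 100 reference subjects that is about 4, with a range from the one already enrolled up to about 20. At the current mix the patients would contribute 50 × 17/22 ≈ 39 (AF) and 50 × 6/15 = 20 (HF).

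The external test set is 20% of 200 = 40 subjects, or about 13 per class. The chance that its 13 reference subjects include nobody aged 65+ is 0.96^13 = 0.59 at a 4% share and 0.80^13 = 0.055 at a 20% share.

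**3. Preliminary model result, as context only.** Table 2 gives sensitivity 11/25 = 44.0% and specificity 33/40 = 82.5%, so balanced accuracy is 63.25%. In Table 1, calling everyone aged 65+ AF gives 17/22 = 77.3% and 24/25 = 96.0%, so balanced accuracy is 86.6%.

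The 22 analysed subjects' ages are not given. Assuming they are among the 62, the least favourable choice of 7 AF and 15 reference subjects gives the age rule these balanced accuracies:

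- cutoff 40: (7/7 + 6/15)/2 = 70.0%
- cutoff 55: (5/7 + 9/15)/2 = 65.7%
- cutoff 65: (2/7 + 14/15)/2 = 61.0%, which is below 63.25%. Of 100,000 random subsets, 99.95% exceed it at this cutoff.

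**4. What redirecting recruitment could achieve.** Suppose the 75 open reference places were filled 0/9/15/51 across the four bands, for a final mix of 16/12/20/52.

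- AF vs Ref: [2 × 22 + 3 × 38 + 17 × 74] / (22 × 100) = 1416/2200 = 0.64.
- HF vs Ref: [1 × 8 + 3 × 22 + 5 × 38 + 6 × 74] / (15 × 100) = 708/1500 = 0.47.
- Pooled: (1416 + 708)/3700 = 0.57, down from 0.90.

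**The case against.** **Stronger inferences that the documents do not support.** From step 3 a reader might infer that age beats the study's own model, or that the model has learned age. Table 2 classifies person-weeks in 22 subjects of unstated age. The age rule classifies persons and is scored on the data that supplied its cutoff. Table 2 comes from MILES applied to preselected recovery curves, reported as a preliminary finding, and not from the planned two-stage model. There is no HF or three-class result to compare with. Age is not a listed input, so nothing shows that MILES picked it up. All of this stands, and the comparison carries no weight in the conclusion.

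**The curves are partly protected.** Each subject's curves are rescaled by that subject's own mean peak and limited to light activity. This weakens explanations based on heart rate level or inactivity. It does not remove an age difference in the speed of recovery, and the slower recovery is one of the two reported differences.

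**The article is aware of subject differences.** It recognises variability from physical attributes, and the Discussion undertakes to examine and mitigate it. That variability is treated as a difficulty in generalising to new subjects, not as something tied to class. An age-only benchmark may well be left to a fuller document, so its absence is not the defect. The recruitment and test-set rules are stated, and Table 1 shows what they have produced. Later adjustment has little to work with when one reference subject is 65 or older.

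**Early data.** Only 62 of 200 are included and the share of 1/25 is imprecise. That is fair, and it is why the projection is given as a range. But no stated rule would correct the imbalance.

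**The reference criterion.** The Abstract and Methods wordings differ. The two subjects listed with hypertension are not a proven breach: blood pressure is measured at the study visit, and Table 1 does not say whether the entry means history or measurement.

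**Conclusion.** The concern holds for disease versus healthy. In the subjects enrolled so far, age band alone separates reference subjects from AF (0.94), from HF (0.84) and from both together (0.90). The stated recruitment, fold and test-set rules leave that imbalance in place. If the plan is followed as written, a disease signal cannot be told apart from an age signal, and this includes the recovery-curve difference offered as an AF indicator. AF versus HF is much less affected (0.69).

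The conclusion rests on Table 1 being roughly representative of later recruitment and on wearable signals depending to some extent on age. The article does not quantify that dependence. It does not show that any wearable finding is due to age, only that the design cannot rule it out.

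**What to change.** 1. Reconcile the reference criterion in the Abstract and in Study design and data collection with the two reference subjects listed with hypertension, so that one definition governs recruitment. Then direct the 75 open reference places toward the age and sex mix of the AF and HF groups as far as feasible.
2. Draw the external-test reference subjects to resemble the patients' age mix, as far as such subjects are available.
3. Report an age-and-sex-only model on the same folds and the same unit of prediction as the benchmark for the wearable model to beat, and give sensitivity and specificity within age bands, for example 55 and over.
4. Until then, describe the recovery-curve difference as not yet separated from age.

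The cost is mainly time. The illustrative mix needs 51 of the 75 remaining volunteers to be 65 or older, which is demanding under a criterion of no history and no medication. It would still leave an age-only AUC of 0.64 for AF versus reference. Matching may therefore be only partial, which makes item 3 necessary as well. Item 3 needs no new data collection.
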